#### Concomitant medications

Enrolled study participants may continue use of all concomitant medications, including prescription, non-prescription, traditional, and other preparations during this study. Participants will be encouraged to avoid douching and the use of vaginally-applied medications/preparations. All concomitant medications used by participants throughout the course of the study will be reported on applicable case report forms (CRFs).

### Safety monitoring and adverse event reporting

#### Adverse events and reporting requirements

An AE is defined as any untoward medical or social occurrence in a clinical research participant which may or may not have a causal relationship with tenofovir gel. Study participants will be provided with contact telephone numbers and instructed to contact study staff to report any AEs they may experience, except for life-threatening events for which they will be instructed to seek immediate emergency care. All participants reporting an AE will be followed clinically until the AE resolves or stabilizes. AEs that are ongoing at the time of study exit will be followed up for up to 30 days after study exit and then, if not resolved, will be referred to a health care provider for further follow-up.

For each AE, an assessment of the relatedness to the study product will be made using the criteria and scale as outlined in the study specific procedures manual and graded for severity using the most current National Institutes for Health Division of AIDS severity grading system. All AEs will be reported on the appropriate CRF and will contain at least the date the AE occurred, a brief description of the event, the relationship to study product, the action taken, the outcome, date resolved, and the seriousness of the event.

#### Serious adverse event reporting

A SAE includes any experience that is fatal or life-threatening, results in persistent or significant disability/incapacity, requires or prolongs hospitalization, or is a congenital anomaly. A life-threatening AE means that the participant was, in the view of the designated study staff, at immediate risk of death from the condition as it occurred. All SAEs will be reported on the appropriate CRF and, with permission of the participant, records from all non-study medical providers related to SAEs will be obtained and required data elements will be recorded on study CRFs. Notification of deaths will be recorded by reflecting the medical condition that led to the death on the appropriate CRF. Reporting SAEs may require additional detailed reports and follow-up. All SAEs will be reported to CONRAD, the South African MCC and the UKZN BREC.

#### Data and safety monitoring

The study statisticians will prepare routine study progress reports which include reports of AEs experienced by study participants for review by the Data and Safety Monitoring Board (DSMB). DSMB members will meet in person and/or via teleconference throughout the period of study implementation to conduct interim reviews of study progress across both arms, including rates of participant accrual, retention, completion of primary and relevant secondary endpoint assessments, and clinical and laboratory adverse events including the SAE rate. Any deaths of study participants or other SAEs will be reviewed and the final decision taken by the DSMB documented. Following review of the data during the trial, the DSMB may recommend that the study proceed as designed, proceed with design modifications, or be discontinued.

### Statistical considerations

#### Primary and secondary endpoints

The primary endpoint for this study is mean gel use, assessed by the number of returned used applicators per participant per month. This endpoint was chosen because the CAPRISA 004 trial demonstrated a correlation between the number of returned used applicators and the level of effectiveness against HIV infection. The following secondary endpoints will be assessed: clinical and laboratory adverse event and pregnancy rates; HIV incidence rates; self-reported adherence to the tenofovir gel dosing strategy; self-reported service acceptability and completion rates of quarterly HIV and pregnancy testing; HIV viral load among HIV seroconverters; tenofovir resistance among HIV seroconverters; vaginal cytokines; HSV-2 and human papilloma virus incidence rates; tenofovir levels (and their correlation with HIV and HSV-2 infection rates); self-reported product acceptability.

#### Power and sample size

A maximum of 700 women, randomized in a 1:1 ratio, will be enrolled over approximately 12 months. We would like to demonstrate that the difference in gel use is no greater than 20% between the two study arms. Since the mean number of returned used applicators in CAPRISA 004 was five per participant per month, a 20% difference in gel use equates to one used applicator per participant per month. A maximum sample size of 700 provides >90% power to demonstrate whether gel use in women attending family planning services is similar to, but no more than 20% lower, than gel use by women attending the CAPRISA research clinics, adjusted for 10% loss to follow-up.

#### Data analysis

The primary objective of this non-inferiority study is to demonstrate that gel use, as measured by the mean number of returned used applicators per participant per month, in the family planning arm is not more than 20% lower than the CAPRISA clinic arm. The number of used applicators returned will be compared between the two treatment arms using an appropriate longitudinal method, such as generalized estimating equations or linear mixed models, adjusted for site. A one-sided test will be used to determine whether the difference in mean gel use between the intervention arm and the control arm is less than 20%.

Analyses will be performed on an intention-to-treat (ITT) basis and on the per-protocol and as-treated populations. For the ITT analysis, participants will be analyzed according to the study arm, even if the participant did not follow the assigned procedures. Because the ITT analysis could increase the chances of declaring equivalence in a non-inferiority study, per-protocol analyses will also be conducted and compared to the ITT analyses before the decision is made to regard the ITT population as the primary population.

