## Methods

### Study design

This is a two-arm, open-label, randomized controlled non-inferiority trial.

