#### Randomization

Enrolled participants will be assigned at random to one of the two study arms in a 1:1 ratio. The randomization list used to assign individual study participants to one of the two arms will be generated by a randomization statistician who is not otherwise involved in the study. This statistician will use a randomly permuted block design, stratified by site. The randomization statistician will provide the site with sealed, opaque randomization envelopes, sequentially labeled by a unique participant identifier. These envelopes will be assigned in sequential order to eligible study participants. Study arm allocation will be concealed until after a participant is deemed eligible to participate in the study. This is an open label trial, and there will be no blinding after the envelope is opened. After completion of randomization procedures, participants who are randomized to the intervention arm will be escorted to the family planning clinic for adherence counseling and gel dispensation.

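### The primary population is to be decided after the ITT and per-protocol results have been compared, with no criterion, so control of the one-sided type I error is not guaranteed

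*Protocol article*

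**What the plan says.** The protocol article describes the design as follows: "This is a two-arm, open-label, randomized controlled non-inferiority trial". Under Primary and secondary endpoints it states: "The primary endpoint for this study is mean gel use, assessed by the number of returned used applicators per participant per month". Under Power and sample size the margin is 20%, and "a 20% difference in gel use equates to one used applicator per participant per month".

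The Data analysis section plans three populations: "Analyses will be performed on an intention-to-treat (ITT) basis and on the per-protocol and as-treated populations". It gives a reason for not relying on ITT alone: "Because the ITT analysis could increase the chances of declaring equivalence in a non-inferiority study". It then says that per-protocol analyses will also be done and "compared to the ITT analyses before the decision is made to regard the ITT population as the primary population".

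No other section names a primary population, gives a criterion for this decision, or says whether non-inferiority must be shown in both sets. The per-protocol set is not defined in the article.

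**The concern.** A confirmatory non-inferiority claim needs its population, or its rule for combining populations, fixed before the arms are compared. Here the article itself places the decision after both comparisons are available. This is more than detail left to an analysis plan: a plan that fixed the population in advance would contradict the sentence as it stands.

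Two things are at stake. First, with no rule for disagreement, the same data could support opposite conclusions depending on which set is called primary, and the one-sided error rate cannot be shown to equal its nominal value. Second, the endpoint is itself a measure of adherence. If membership of the per-protocol set depended on gel use or visit attendance, the set would be conditioned on the outcome and could hide the deficit that the trial is meant to detect.

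**Working it through.** **Inputs from the article.** Maximum 700 women, 1:1, so 350 per arm. With 10% loss to follow-up, 350 × 0.90 = 315 per arm. Since "the mean number of returned used applicators in CAPRISA 004 was five per participant per month", the margin is 0.20 × 5 = 1 applicator per month. The test is one-sided and the stated power is above 90%.

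**Assumptions.** Alpha and the standard deviation (SD) are not given. I use one-sided alpha of 0.025 and 0.05, and leave the SD free.

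**1. The plan's own figure.** Power is 90% when margin / (SD × √(2/315)) = z(1−α) + z(0.90), so the largest SD that gives 90% is 1 / [(z(1−α) + 1.282) × √(2/315)].
- α = 0.025: 1 / (3.242 × 0.0797) = 3.87.
- α = 0.05: 1 / (2.926 × 0.0797) = 4.29.

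The stated power holds if the SD is no larger than these values. It can be neither confirmed nor refuted, and the point does not depend on it.

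**2. Type I error under three possible rules.** Put the true difference exactly at the margin in both sets, with no selection bias. The ITT and per-protocol test statistics are then bivariate standard normal with correlation √s, where s is the per-protocol share of the ITT set. A single pre-fixed set gives α. For the other two rules, P(either passes) = 2α − P(both pass).

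| s | √s | either, α = 2.5% | both, α = 2.5% | either, α = 5% | both, α = 5% |
|---|---|---|---|---|---|
| 0.9 | 0.949 | 3.2% | 1.8% | 6.3% | 3.7% |
| 0.8 | 0.894 | 3.5% | 1.5% | 6.9% | 3.1% |
| 0.7 | 0.837 | 3.8% | 1.2% | 7.3% | 2.7% |
| 0.6 | 0.775 | 4.0% | 1.0% | 7.7% | 2.3% |

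The article's wording does not say which column applies.

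**3. Conditioning on the outcome (illustration; all rates assumed).** Suppose that 30% of family planning women and 10% of controls use no gel, that users in both arms use equal amounts, and that non-users are excluded from per-protocol.
- ITT ratio: 0.70 / 0.90 = 0.78. With a control mean of 5, the family planning mean is 5 × 0.70 / 0.90 = 3.89, a deficit of 1.11, outside the margin of 1.
- Per-protocol ratio: 1.00, because only users remain.

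With 10% non-users among controls, the ITT ratio falls below 0.80 only when family planning non-users exceed 1 − 0.80 × 0.90 = 28%. A smaller imbalance, such as 20% against 10% (0.80 / 0.90 = 0.89), moves the estimate but stays inside the margin, so it would not produce a false claim.

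**4. Power if both sets must pass.** Start at exactly 90% ITT power with no true difference. The per-protocol statistic has mean √s times that of ITT, and the correlation is √s.
- s = 0.9: joint power about 86% at either alpha.
- s = 0.8: joint power about 81% (α = 0.025) or 82% (α = 0.05).
- At an SD of 3, where ITT power is about 99%, joint power is 96% or more in all these cases.

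**The case against.** The strongest reply is that the stated motive is conservative. The sponsor fears that ITT favours non-inferiority and wants to see per-protocol before relying on it. The only decision named is whether to regard ITT as primary; nothing says that per-protocol may replace a failed ITT. A natural reading is that ITT is accepted if per-protocol agrees, and if that amounts to requiring both, the error is below nominal.

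This reply stands in part. A reader might infer that type I error is inflated, or that the sponsor intends to name the passing set; the article supports neither. It does not remove the point, because the agreeing-sets reading is not written down either, and nothing says what happens when the sets differ.

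A reader might also infer that the per-protocol set will drop women who do not use gel. The article does not define the set. Not following assigned procedures is mentioned only when ITT is described, and the definition may properly sit in the full protocol or analysis plan. The illustration is therefore conditional.

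Finally, the open-label design ("This is an open label trial, and there will be no blinding after the envelope is opened") is not the cause. The same defect would exist in a blinded trial once results by arm had been compared.

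**Conclusion.** The point holds as a lack of guaranteed control. The article makes the choice of primary population follow the comparison of results, without a criterion and without a rule for disagreement.

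The size depends on a rule that is not stated. At worst, one-sided error rises to about 1.3 to 1.6 times nominal (3.2/2.5 to 4.0/2.5). At best, if both sets are required, it stays at or below nominal. These figures assume normal test statistics, a true difference at the margin in both sets, no selection bias, per-protocol shares of 90% to 60%, and alpha levels that the article does not give. Conditioning on gel use could matter more, but only if the per-protocol set is defined that way and non-use differs strongly between arms. Confidence is high on what the sentence says and lower on its consequence.

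**What to change.** Delete the late decision and state one rule before any comparison by arm is seen. Trial status says that enrolment is ongoing, so this appears still possible. Either rule below closes the gap; the text should contain only one.

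**Option A, which answers the sponsor's own worry about ITT.** Suggested wording: *Non-inferiority will be claimed only if the one-sided confidence limit for the difference in mean gel use clears the margin in both the ITT and the per-protocol populations. Membership of the per-protocol population will be defined in advance and will not depend on gel use.* The same caution applies to visit attendance. The error cannot exceed nominal if the true difference is at or beyond the margin in either set. If ITT power is exactly 90%, the cost is a fall to about 86% with 10% excluded or 81% to 82% with 20% excluded; the loss is smaller if power is well above 90%.

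**Option B.** Suggested wording: *The ITT population is the sole primary population. The per-protocol analysis, with the same margin, is supportive and does not alter the primary conclusion.* The cost is wording only. The claim then rests on ITT alone, so the sponsor's concern about ITT is met only by reporting per-protocol beside it.

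Under either option, state the one-sided alpha and say that the as-treated analysis is supportive.

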#### Data management

Data will be collected on standardized CRFs, which will be developed by the study team. Source documents will be maintained in the participant’s medical chart or study file at the site. CRFs will be faxed to the central CAPRISA Data Management Server using the DataFax system (Clinical DataFax Systems Inc., Ontario, Canada). Queries arising during validation of the data will be recorded in quality control reports sent to the sites on a regular basis. The original CRFs and related documents will be stored securely at the sites, both during and after the completion of the study.

### Ethical considerations

#### Regulatory and ethical review

This study is being conducted under the regulatory oversight of the South African MCC (reference number: 20110145) and the ethical oversight of UKZN’s BREC (reference number: BFC 237/010) and in accordance with International Conference on Harmonization guidance and Good Clinical Practice standards. The study was initiated after receipt of approval by the MCC (approval date: 21 May 2012) and UKZN’s BREC (approval date: 13 September 2012). The study is being conducted in accordance with all conditions of approval by the ethics and regulatory committees.

#### Community involvement and consultation

The CAPRISA Community Program has, through a consultative process, established CAPRISA Community Research Support Groups at both the CAPRISA sites where this study will be conducted. The membership of these Community Research Support Groups includes local community leaders, traditional leaders, leadership of local HIV/AIDS organizations, previous study participants, local health service provider representatives and HIV-positive local community members. In preparation for this trial, the CAPRISA Community Program will inform, educate and mobilize the community to enhance community input into the research process.

#### Confidentiality

Every effort will be made to protect participant privacy and confidentiality to the extent permitted by law.

## Discussion

CAPRISA 004 established proof-of-concept that tenofovir gel is safe and effective in preventing HIV infection in a rigorous clinical trial. Translating these findings into health service programs poses many challenges that can be exacerbated in the context of weak health care delivery systems. The post-trial, pre-licensure window is a critical period to prepare and devise effective strategies for informing future policy and programmatic scale-up of new interventions. CAPRISA 008 will answer important implementation questions about how best to incorporate tenofovir gel into routine family planning health services in South Africa and how to make it accessible to women who would benefit most from this product. By undertaking this study now, prior to licensure, stakeholders will be better prepared for widespread roll-out and scaling up of provision of tenofovir gel within the public health system of South Africa.

This study will also add to the growing body of implementation research for HIV prevention. Implementation science uses the scientific method to investigate how to integrate research findings and evidence-based interventions into health care policy and practice [39]. Several recent studies have generated useful data for guiding the implementation of programs to reduce mother-to-child transmission of HIV and increase uptake of medical male circumcision for HIV prevention [40–43]. However, CAPRISA 008 is the first study to evaluate implementation strategies for an HIV prevention tool that can be used by women to protect themselves from infection over a long period of time.

There is increasing consensus that research participants in developing countries should have post-trial access to beneficial interventions based on the ethical principles of beneficence and justice [44]. During the waiting period for confirmatory studies and the licensure of tenofovir gel, CAPRISA has a responsibility to make the gel available to CAPRISA 004 participants since it is unavailable to them through any other channel. By inviting CAPRISA 004 participants to take part in the CAPRISA 008 study, we are able to meet this post-trial ethical obligation whilst generating important data for the future implementation of tenofovir gel within the health service.

## Trial status

Participant recruitment, screening and enrollment are ongoing.

## Abbreviations

AE: adverse event
ARV: antiretroviral
BREC: Biomedical Research Ethics Committee
CAPRISA: Centre for the AIDS Programme of Research in South Africa
CRF: case report form
DSMB: Data and Safety Monitoring Board
FTC: emtricitabine
HSV-2: herpes simplex virus type 2
ITT: intention-to-treat
MCC: Medicines Control Council
PCZCDC: Prince Cyril Zulu Communicable Disease Centre
PHC: primary health care
QI: quality improvement
SAE: serious adverse event
STI: sexually transmitted infection
TDF: tenofovir disoproxil fumarate
UKZN: University of KwaZulu-Natal.
